## Abstract

**Introduction:**

During cardiopulmonary bypass (CPB), impaired perfusion, ischemia–reperfusion injury, and systemic inflammation frequently result in lactate accumulation. Lactate is routinely monitored perioperatively and may serve as an early indicator of postoperative infection, yet prospective evidence linking intraoperative lactate to infection risk remains limited. This prospective cohort study aims to evaluate the association between the time-weighted average (TWA) lactate during CPB and the risk of postoperative infection in patients undergoing cardiac surgery.

**Methods:**

This single-center, prospective cohort study will enroll 346 adult patients undergoing elective cardiac surgery with CPB. Arterial blood samples will be obtained at multiple intraoperative time points to calculate TWA lactate. Patients will be classified into exposure and non-exposure groups based on a TWA lactate cutoff of ≥2.0 mmol/L. The primary outcome is the incidence of infection within 30 days of surgery. A predefined directed acyclic graph will guide covariate adjustment. Multivariable logistic regression will estimate the risk association, and restricted cubic spline models will explore potential nonlinear relationships. Sensitivity analyses will use lactate load, defined as the area under the lactate–time curve during CPB, to examine whether cumulative intraoperative lactate exposure yields results consistent with those obtained using TWA.

**Discussion:**

This prospective cohort study aims to investigate the association between time-weighted average lactate during cardiopulmonary bypass and postoperative infection risk in cardiac surgery patients. If the hypothesis is confirmed, TWA lactate could serve as a readily available marker for intraoperative risk stratification, facilitating early identification of high-risk patients and guiding individualized interventions. The findings may provide evidence for optimizing perioperative management and improving clinical outcomes. As a single-center study, external validation in multicenter settings will be needed to enhance generalizability.

**Clinical Trial Registration:**

https://www.chictr.org.cn, identifier ChiCTR2500110269.

## Introduction

1

Cardiovascular disease remains the leading cause of death and disability worldwide, causing 19.2 million deaths globally in 2023 (1). Cardiopulmonary bypass (CPB)-assisted cardiac surgery is a common and effective clinical intervention (2, 3); however, the pathophysiological alterations induced by CPB markedly increase the incidence of perioperative complications, particularly postoperative infections (4). The major types of postoperative infections include sepsis, pulmonary infection, surgical site infection, mediastinitis, and infective endocarditis (5). These complications have contributed to increased healthcare costs, prolonged hospitalization, and poorer patient outcomes. Therefore, identifying early and measurable risk markers is of great clinical significance in reducing postoperative infections, mortality and healthcare resource utilization.

Serum lactate is a complex biomarker. Lactate levels during CPB surgery typically serve as an indicator of overall physiological stress, surgical complexity, and perfusion adequacy (6, 7). The nonpulsatile perfusion pattern during CPB can lead to organ hypoperfusion, ischemia–reperfusion injury, and systemic inflammatory responses, all of which may enhance lactate metabolism and cause peripheral lactate accumulation (8, 9). In this study, we hypothesize that lactate serves as both a marker of underlying pathophysiological processes and a potential mediator of immunosuppression. At high concentrations (e.g., 12.5 mM), it enhances hypoxia-inducible factor 1-alpha (HIF-1*α*) expression, while mitigating acute inflammatory injury, which also suppresses mast cell activation via monocarboxylate transporter 1 (MCT-1) and pH-dependent pathways, thereby increasing the risk of infection (10). Furthermore, lactate impairs T-cell function by inhibiting migration, reducing the cytotoxic activity of neutrophil, cluster of differentiation 4-positive T cells (CD4^+^) and cluster of differentiation 8-positive T cells (CD8^+^) T cells, promoting CD4^+^ T cell differentiation toward the T helper 17 cells (Th17) subset, and inducing interleukin-17 (IL-17) accumulation, collectively leading to the occurrence of surgical site infections and other infections (11, 12). In sepsis, lactate is closely associated with diagnosis, progression, and treatment, and it further reduces immune cell activity by inducing mitochondrial dysfunction and impaired oxygen consumption, contributing to multiple organ dysfunction (13). Lactate can also suppress nuclear factor *κ*B (NF-*κ*B) transcriptional activity and cytokine production in mast cells, whereas enhancing glycolysis and adenosine triphosphate (ATP) generation can restore immune function (14). Previous studies have also indicated that acidification is an independent virulence mechanism for pneumonia barrier disruption and inflammatory dysregulation, which may directly contribute to the development and progression of bacterial pneumonia, whereas maintaining normal pH represents an effective therapeutic strategy for preserving barrier integrity and immune response (15). Based on the above evidence, a mechanistic diagram (Figure 1) was constructed to integrate these proposed mechanisms and illustrate how cardiopulmonary bypass-related lactate elevation may promote postoperative infection through lactate-mediated immune dysregulation. Because lactate measurement is inexpensive, reproducible, and routinely monitored during the perioperative period, it has inherent advantages as a potential biomarker for postoperative infection risk.

**Figure 1 F1:**
[figure not shown]
Proposed mechanism by which TWA lactate during cardiopulmonary bypass induces immunosuppression leading to postoperative infection. During cardiopulmonary bypass, non-pulsatile perfusion, organ hypoperfusion, ischemia–reperfusion injury, and systemic inflammatory activation may promote serum lactate accumulation. Elevated lactate may subsequently contribute to perioperative immune dysregulation through several mechanisms, including AARS1/2-mediated lactate sensing and cGAS lactylation, suppression of T-cell migration and cytotoxic function, promotion of CD4⁺ T-cell differentiation toward the Th17 subset, impairment of mast-cell function in a pH-dependent microenvironment, and mitochondrial dysfunction with reduced oxygen consumption in immune cells. Collectively, these lactate-related immunosuppressive effects may create a favorable environment for pathogen colonization and dissemination, thereby increasing the risk of postoperative infectious complications, including pneumonia, surgical site infection, mediastinitis, infective endocarditis, and sepsis. TWA, time-weighted average; CPB, cardiopulmonary bypass; AARS1/2, alanyl-tRNA synthetase 1/2; CD4⁺ T-cell, cluster of differentiation 4-positive T cell; CD8⁺ T-cell, cluster of differentiation 8-positive T cell; cGAS, cyclic GMP-AMP synthase; HIF-1*α*, hypoxia-inducible factor-1*α*; Th17, T helper 17 cell.

Currently, studies on the association between lactate levels and the risk of postoperative infection in cardiac surgery are limited and the evidence is insufficient. Studies on lactate and cardiac surgical outcomes have primarily focused on organ dysfunction, mortality, intensive care unit (ICU) length of stay, and postoperative mechanical ventilation time (16, 17). In the field of infection research, investigations of lactate have mainly centered on its role in assessing sepsis severity and prognosis (18). Moreover, a retrospective study of adult cardiac surgery found that there was no significant difference in the incidence of postoperative infection between the high lactate group and the low lactate group (19). However, another more recent retrospective study found that patients with postoperative pneumonia had significantly higher perioperative lactate levels than those without pneumonia (20). Therefore, in this particular population of cardiovascular surgery patients, the lactate levels during surgery and the incidence of various types of postoperative infections, such as pulmonary infection, surgical site or mediastinal infection, and infective endocarditis, still lack large-scale prospective cohort studies.

In patients undergoing cardiac surgery with CPB, evaluating the predictive value of lactate exposure during CPB as an early warning indicator for postoperative infection may help address current evidence gaps. It can provide a scientific basis for perioperative management, early infection identification, and individualized prevention strategies, thereby reducing complication rates and healthcare burdens. Therefore, the relationship and predictive value between lactate and postoperative infection warrant validation through larger, prospective cohort studies, underscoring the clear clinical and scientific significance of the present research.

This study is a single-center, prospective cohort study designed to investigate the association between time-weighted average (TWA) lactate levels during CPB and postoperative infection in patients undergoing cardiac surgery. The null hypothesis of this study is that the time-weighted average lactate level during CPB is not associated with postoperative infection in patients undergoing cardiac surgery with CPB.

## Methods

2

### Study design and setting

2.1

This study is a single-center, prospective cohort study. It is planned to be conducted at the Affiliated Hospital of Qingdao University. Participants will be categorized into an exposure group based on a TWA lactate level ≥2.0 mmol/L and followed for 30 days postoperatively to assess the occurrence rate of postoperative infections (Figure 2). This trial was approved by the Medical Ethics Committee of the Affiliated Hospital of Qingdao University (Approval No. QYFYEC2025-147). Prior to study initiation, written informed consent will be obtained from all participants. This study will be conducted in accordance with the Declaration of Helsinki. The trial has been prospectively registered with the Chinese Clinical Trial Registry (ChiCTR2500110269, available at https://www.chictr.org.cn, prospectively registered on October 11, 2025).

**Figure 2 F2:**
[figure not shown]
Study flow diagram.

### Eligibility criteria

2.2

#### Inclusion criteria

2.2.1

Age ≥18 years; 2. Patients undergoing elective open cardiac surgery with CPB, such as coronary artery bypass grafting, valve replacement or repair, artificial vascular replacement, cardiac tumor resection, other, and combined surgery, such as valve replacement combined with coronary artery bypass grafting.

#### Exclusion criteria

2.2.2

History of previous cardiac surgery requiring sternotomy and/or CPB; 2. Emergency surgery; 3. Presence of any type of preoperative infection (e.g., preoperative pneumonia, infective endocarditis); 4. Severe hepatic or renal dysfunction (e.g., jaundice, coagulation disorders, hepatic encephalopathy, serum creatinine >442 μmol/L, blood urea nitrogen >20 mmol/L, or requiring dialysis); 5. Preexisting immunodeficiency disorders (e.g., HIV infection, use of immunosuppressive drugs, autoimmune diseases).

### Sample size calculation

2.3

Previous studies have reported that the incidence of postoperative infection after cardiovascular surgery is approximately 10.4%–15.5% (21–23). To obtain a conservative sample size estimate and avoid overestimating the expected event rate, we used the lowest reported incidence of 10.4% as the baseline infection rate in the normal lactate group. The same study that reported this baseline incidence also reported an odds ratio (OR) of 2.75 for postoperative infection in the high-lactate group compared with the normal-lactate group (21). With a two-sided *α* of 0.05 and a power of 0.9, the required sample size per group was estimated to be 156 using PASS 2021 software (NCSS, LLC, Kaysville, UT, USA), resulting in a total sample size of 312. Considering a 10% loss to follow-up, at least 173 participants per group are needed, for a total of 346 participants.

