### Statistical analysis

2.9

Data with a normal distribution will be expressed as mean ± standard deviation (SD), non-normally distributed data as median and interquartile range (IQR), and categorical variables as frequency (n) and percentage (%). Baseline data will be compared using two-sample t-tests, Mann–Whitney U tests, or chi-square tests. Univariate logistic regression analysis will be used to evaluate the association between TWA lactate, covariates, and postoperative infection, calculating odds ratios and 95% confidence intervals (95% CI). The following are the primary analyses: according to the DAG (Figure 4), confounders that are common causes of both TWA lactate and postoperative infection will be adjusted for, whereas mediators and colliders on the causal pathway will not be adjusted. In the model, TWA lactate will be analyzed as both a categorical variable and a continuous variable. Multivariable logistic regression will be employed to assess the risk association between TWA lactate and postoperative infection, reporting adjusted odds ratios (aOR) and 95% CI. For the continuous analysis, aOR will be reported per 0.5 mmol/L increase, per 1.0 mmol/L increase, and per 1-standard deviation increase in TWA lactate. For the categorical analysis, TWA lactate will be dichotomized according to the prespecified cutoff of 2.0 mmol/L. The median of tertiles will be used as a quasi-continuous variable to analyze the linear trend between TWA lactate and postoperative infection risk. Restricted cubic spline regression will be applied to explore the potential nonlinear relationship between TWA lactate and postoperative infection. Threshold analysis will be performed using segmented regression, and the likelihood ratio test will be applied to compare the goodness-of-fit between linear and nonlinear models to identify the optimal model. Based on the determined threshold, an adjusted segmented linear regression model will be constructed to estimate aOR and 95% CI before and after the threshold. The following are the secondary analyses: prespecified subgroup analyses will be conducted according to key characteristics, including age, sex, preoperative comorbidities, and surgery type, and interaction effects will be evaluated. To assess robustness, we will perform sensitivity analyses using lactate load and peak lactate during CPB, and repeat the statistical analyses. To control the error of type I due to multiple comparisons, *P* values for secondary outcomes and prespecified subgroup interaction tests will be adjusted using the Holm–Bonferroni method. All statistical tests are two-sided, and *P* < 0.05 is considered statistically significant.

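### The 90% power in section 2.3 holds only for an unadjusted comparison of two equal groups at 10.4% versus 24.2%, which is neither the cohort nor the primary analysis that the plan describes

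*Protocol article*

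**What the plan says.** Section 2.3 (Sample size calculation) states that "the incidence of postoperative infection after cardiovascular surgery is approximately 10.4%–15.5"%, which describes cardiac surgical patients as a whole. It then gives its reason, "To obtain a conservative sample size estimate and avoid overestimating the expected event rate", and its choice: "we used the lowest reported incidence of 10.4% as the baseline infection rate in the normal lactate group". The study that supplied the 10.4% "also reported an odds ratio (OR) of 2.75 for postoperative infection in the high-lactate group compared with the normal-lactate group". With two-sided α of 0.05 and "a power of 0.9, the required sample size per group was estimated to be 156 using PASS 2021 software", the total is 312. After 10% loss, "at least 173 participants per group are needed, for a total of 346 participants".

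The abstract and section 2.4 (Exposure) describe one cohort of 346, divided afterwards by measured TWA lactate at 2.0 mmol/L. They give no quota per group and no expected exposed share.

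For the primary analysis, section 2.9 says "Multivariable logistic regression will be employed to assess the risk association between TWA lactate and postoperative infection", with adjusted odds ratios. Section 2.6 lists the adjustment set. It includes preoperative lactate, CPB time and cross-clamp time, and the plan describes the set as common causes of raised lactate and of infection.

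**The concern.** Three inputs to the calculation do not match the rest of the plan.

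- **Event rate.** A figure introduced as the lower end of an overall incidence is assigned to the unexposed group alone. The exposed group is then set higher, so the overall rate rises above the figure that was meant to be cautious.
- **Group sizes.** The calculation needs equal groups, but only the total is under the investigators' control.
- **Analysis.** The calculation compares two crude proportions. The planned test is of a coefficient adjusted for variables that the plan itself treats as causes of the exposure, and that correlation costs precision.

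The stated power governs how a null result will be read. The introduction notes that earlier retrospective studies disagree on lactate and infection. A non-significant result from a study described as having 90% power would be taken as fairly strong evidence against an odds ratio of 2.75. That reading is justified only under the conditions of the calculation.

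**Working it through.** **Inputs from section 2.3:** two-sided α 0.05, power 0.90, unexposed rate p₁ = 0.104, OR 2.75, 1:1 groups, 312 evaluable, 346 enrolled. **Assumed, because the article does not give them:** the exposed share f (20% to 80%), and R², the proportion of exposure variance explained by the covariates (0.1 to 0.3).

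**1. Reproducing the plan's figure.**

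p₂ = OR·p₁ / (1 − p₁ + OR·p₁) = 0.286 / (0.896 + 0.286) = 0.242.

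Two-proportion z-test, with pooled variance under the null, unpooled under the alternative, and no continuity correction:

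n = [1.960·√(2p̄(1−p̄)) + 1.282·√(p₁(1−p₁) + p₂(1−p₂))]² / (p₂−p₁)²

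With p̄ = 0.173 the two roots are 0.5349 and 0.5259, and p₂−p₁ = 0.1380. This gives n = 155.9, so 156 per group, with power 90.0%. The plan's figure is matched exactly by this unadjusted, equal-group formula.

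**2. Implied overall incidence.** At 1:1 it is (10.4% + 24.2%)/2 = 17.3%, or about 54 events in 312. The cited maximum is 15.5%, or about 48 events.

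**3. Power with overall incidence held in the cited range.** For each overall rate, p₁ is solved so that (1−f)·p₁ + f·p₂ equals that rate with OR 2.75. N = 312, unadjusted.

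| Overall rate | Unexposed vs exposed at 1:1 | Power at 1:1 | Best power at any share | OR detectable with 90% power, 1:1 |
|---|---|---|---|---|
| 10.4% | 6.0% vs 14.8% | 73.1% | 76.7% | 3.7 |
| 13% | 7.6% vs 18.4% | 81.5% | 83.9% | 3.2 |
| 15.5% | 9.2% vs 21.8% | 87.1% | 88.7% | 2.9 |

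The best shares lie between 36% and 39%. At none of these rates does any split reach 90%.

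**4. Unequal groups at the plan's own rates** (10.4% vs 24.2%, N = 312, unadjusted):

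| Exposed share | 20% | 30% | 40% | 50% | 60% | 70% | 80% |
|---|---|---|---|---|---|---|---|
| Power | 77.9% | 85.9% | 89.3% | 90.0% | 88.4% | 83.1% | 69.5% |

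**5. Adjustment at 1:1**, approximated by an effective sample size of N·(1−R²):

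| Assumed R² | Plan's rates (17.3% overall) | 15.5% overall | 10.4% overall |
|---|---|---|---|
| 0.1 | 86.8% | 83.4% | 68.5% |
| 0.2 | 82.6% | 78.9% | 63.4% |
| 0.3 | 77.3% | 73.3% | 57.6% |

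A simulated adjusted logistic regression (1,500 runs per scenario, one prognostic covariate, R² about 0.16, 1:1) gave about 82%, 77% and 62% at 17.3%, 15.5% and 10.4% overall. This agrees with the approximation.

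**The case against.** The arithmetic in section 2.3 is sound: 156 per group reproduces exactly. The objections concern the inputs, and several have force.

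- **The 10.4% may be a normal-lactate rate.** Section 2.3 later calls it a baseline incidence, from the same study that compared high with normal lactate. The cited source is not at hand, so this cannot be settled. If it is a normal-lactate rate, the low end is indeed the cautious choice for that group: 15.5% there would need only about 118 per group. The 73% to 87% figures are therefore conditional on the range being an overall incidence, as the section's first sentence presents it.
- **The 17.3% depends on the 1:1 split.** At the plan's own rates the overall figure stays within 15.5% for any exposed share up to (15.5 − 10.4)/(24.2 − 10.4) = 37%, where power is still 89%. This stands. It escapes the first inconsistency only by giving up the equal groups on which the calculation rests.
- **Some departures are trivial.** An exposed share of 40% or 60%, without adjustment, costs 1 to 2 points. With no loss at all, 346 evaluable would give 92.7%, or 90.0% with R² of 0.1; the plan itself expects 10% loss.
- **Confidence intervals will be reported, and TWA lactate is also analysed as continuous.** Both soften the consequence. Neither makes the 90% apply, since it was not calculated for the continuous analysis.

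A reader might go further and infer that the study is shown to be badly underpowered, with some definite lower power. The article does not support that, because it gives neither the exposed share nor the exposure–covariate correlation. A reader might also object that 156/0.9 = 173.3 should round up to 174 per group. That is immaterial: 346 less 10% leaves 311 evaluable, with power 89.9%.

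**Conclusion.** The concern holds as a mismatch between the stated power and the planned study. The 90% is correct for an unadjusted 1:1 comparison of 10.4% with 24.2%, and it is not established for the planned cohort and adjusted model.

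If 10.4%–15.5% is an overall incidence, the claim to avoid overestimating the event rate fails at 1:1, and 90% is out of reach at any split even before adjustment. If 10.4% is a normal-lactate rate, that criticism falls away and the cited range is mislabelled, but the points on unequal groups and on adjustment remain.

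The mismatch is certain; the size of the shortfall is not. It runs from a point or two to a substantial loss, depending on the exposed share, the overall incidence and R². The article also does not say whether the OR of 2.75 is crude or adjusted. If it is crude, the adjusted effect may be smaller and power lower still.

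**What to change.** Keep 346 and revise section 2.3:

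1. State that 90% power applies to an unadjusted comparison of two equal groups with 10.4% infected in the unexposed group and OR 2.75.
2. State whether 10.4% is an overall or a normal-lactate rate. If overall, remove the description of the choice as conservative and as avoiding an overestimated event rate.
3. Replace the minimum of 173 per group with the total, since group sizes will be observed.
4. Give the expected power of the adjusted analysis over a plausible range of exposed share, overall incidence and R², together with the odds ratio detectable at 90% power (about 2.9 at 15.5% overall to 3.7 at 10.4%, unadjusted at 1:1).

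The cost is the rewording of one paragraph and a less favourable power statement. Enrolment, outcome and analysis do not change.

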### Exposure

2.4

Trained research personnel will measure patients' blood lactate levels during cardiopulmonary bypass using Radiometer ABL90 FLEX blood gas analyzer. The procedures are as follows:
During cardiopulmonary bypass, arterial blood samples will be collected from the radial or femoral artery at the following time points: T_1_, after the initiation of cardiopulmonary bypass, when coronary perfusion with cardioplegic solution induces cardiac arrest; T_2_, T_3_, …, Tn, every 1 h after the start of bypass; T_n_ _+_ _1_, 10–20 min before the end of bypass; and T_n_ _+_ _2_, within 5 min after the end of bypass. Here, T_n_ represents the last full-hour sampling point during bypass. Additionally, extra samples will be collected whenever there is a sudden increase in lactate during CPB (e.g., following hypotension or hypoperfusion events). At least four lactate measurements during cardiopulmonary bypass are required for TWA lactate calculation.Within 1 min of blood collection, lactate levels will be measured using the blood gas analyzer and recorded in mmol/L to one decimal place. If duplicate measurements are performed at the same time point, the mean value will be used as the final lactate measurement.The time-weighted average lactate (TWA) will be calculated from the lactate values obtained at different time points. TWA is defined as the area under the curve of lactate levels over time divided by the total observation interval, using the formula:$$TWA=\frac{1}{T}\overset{n=1}{\underset{i=1}{\sum }}\;\left(\frac{v_{i}+v_{i+1}}{2}\right)\Delta t_{i}$$Evidence from previous cardiac surgery cohort studies has reported that lactate concentration of >2.0 mmol/L during surgery or in the early postoperative period are already associated with increased postoperative morbidity and mortality. Accordingly, based on the available evidence, recommendations from international sepsis guidelines, TWA lactate of 2.0 mmol/L is selected as the prespecified cutoff for exposure classification. TWA lactate ≥2.0 mmol/L during CPB will be categorized into the exposure group, with the TWA lactate <2.0 mmol/L classified into the non-exposure group (24–27). Lactate will also be analyzed as a continuous variable in the subsequent analyses.We will also calculate the following lactate indices to comprehensively characterize lactate exposure:
Peak lactate: The highest lactate value recorded during CPB.Lactate load: The area under the lactate-time curve (AUC) during cardiopulmonary bypass, calculated using the trapezoidal method.24-hour postoperative lactate clearance: [(Lactate at the end of surgery – Lactate at 24 h after surgery)/Lactate at the end of surgery]  ×  100%.

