
### Handling of missing data

2.10

Missing data will be traced and verified, and if they cannot be retrieved, they will be marked as missing in the database. Participants with missing data on the exposure or the primary outcome will not be imputed and will be excluded from the analysis. The proportion and pattern of missing data will be summarized for all variables, including baseline characteristics, covariates, and secondary outcomes.

The missing-data mechanism will be assessed using Little's missing completely at random (MCAR) test. When the data are compatible with MCAR and the variable-specific missingness is below 5%, missing values will be imputed using the k-nearest neighbors (KNN) algorithm. Otherwise, missing values in the minimal adjustment set identified by the DAG and in secondary outcomes will be assumed to be missing at random (MAR) and handled using multiple imputation. The imputation model will include the exposure variable, primary outcome, secondary outcomes, the minimal adjustment set identified by the DAG, and relevant auxiliary variables when available. Multiple imputation will be performed using 20 imputed datasets with a maximum of 50 iterations. Predictive mean matching will be used for continuous variables, while logistic regression will be used for categorical variables. Estimates from the imputed datasets will be combined using Rubin's rules.

As a sensitivity analysis, the primary analysis will be repeated using complete-case data and compared with the results based on multiple imputation. If substantial differences are observed between the two approaches, the potential influence of missing not at random (MNAR) mechanisms on the study findings will be discussed.

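### The four-measurement minimum for TWA lactate cannot be met by the plan's own sampling schedule in bypass runs under 60 min, and the only remedy it provides depends on the exposure

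*Protocol article*

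**What the plan says.** Section 2.4 (Exposure) of the protocol article schedules these arterial samples:

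- T1: "after the initiation of cardiopulmonary bypass, when coronary perfusion with cardioplegic solution induces cardiac arrest".
- T2 to Tn: "every 1 h after the start of bypass", where Tn "represents the last full-hour sampling point during bypass".
- Tn+1: "10–20 min before the end of bypass".
- Tn+2: "within 5 min after the end of bypass".

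In addition, "extra samples will be collected whenever there is a sudden increase in lactate during CPB"; hypotension and hypoperfusion are named as examples of what may precede such a rise. Repeat measurements at one time point are averaged into a single value. The section then sets the minimum: "At least four lactate measurements during cardiopulmonary bypass are required for TWA lactate calculation".

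Section 2.10 (Handling of missing data) states: "Participants with missing data on the exposure or the primary outcome will not be imputed and will be excluded from the analysis". The eligibility criteria in section 2.2 set no lower limit on bypass time. Section 2.3 inflates the sample size by 10%, for loss to follow-up only.

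**The concern.** The minimum and the schedule were not checked against each other. A site that follows the schedule exactly will still produce eligible, consented patients whose TWA may not be calculated. Under section 2.10 they drop out of the analysis.

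The loss is not random. Among short runs, the one route to a fourth sample that the plan provides is a sudden lactate rise, so whether such a patient is analysed depends on the exposure. Those lost are mainly short-run patients without a lactate spike.

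The planned comparison of complete-case and imputed results cannot reveal this, because patients with missing exposure are absent from both analyses. The 10% allowance does not cover them either.

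**Working it through.** **Step 1: the plan's own sample size.** Inputs from section 2.3: p1 = 0.104, OR = 2.75, two-sided α = 0.05, power 0.90.

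- p2 = 0.104 × 2.75 / (1 − 0.104 + 0.104 × 2.75) = 0.286 / 1.182 = 0.2420, so d = p2 − p1 = 0.1380 and the mean proportion is 0.1730.
- n = [1.960 × √(2 × 0.1730 × 0.8270) + 1.2816 × √(0.104 × 0.896 + 0.2420 × 0.7580)]² / d²
- n = (1.0484 + 0.6740)² / 0.1380² = 155.9, hence 156 per group. The plan's figure is reproduced.
- 312 / 0.9 = 346.7, against the stated 346. The difference is rounding and does not matter here.

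**Step 2: scheduled samples by bypass duration D.** All scheduled samples = 1 (T1) + completed hours + 1 (Tn+1) + 1 (Tn+2). Leaving out Tn+2 gives the number taken on bypass.

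| D (min) | T1 | Hourly | Tn+1 | Tn+2 | All | On bypass only |
|---|---|---|---|---|---|---|
| under 60 | 1 | 0 | 1 | 1 | **3** | 2 |
| 60–119 | 1 | 1 | 1 | 1 | 4 | 3 |
| 120–179 | 1 | 2 | 1 | 1 | 5 | 4 |

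With Tn+2 counted, every run under 60 min falls one short, and one triggered sample would make it up.

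**Step 3: coinciding samples.** Tn+1 falls at D − L, with L between 10 and 20 min. It meets the 60-min sample when D − L = 60, so for D between 70 and 80 min. The two are then one time point, and the count is three again. The same coincidence at 130–140 min leaves four and does no harm.

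**Step 4: share affected (assumption).** The documents give no distribution of bypass time and no rate of triggered samples. Assume log-normal bypass time with log-SD 0.4, and that 15% of patients have one triggered sample, independent of duration.

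- Median 90 min: P(D < 60) = Φ(ln(60/90)/0.4) = Φ(−1.014) = 15.5%. Excluded: 0.85 × 15.5% = 13.2%.
- Median 130 min: P(D < 60) = Φ(ln(60/130)/0.4) = Φ(−1.933) = 2.7%. Excluded: 0.85 × 2.7% = 2.3%.

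The range is about 2–13%, before any coincidences at 70–80 min.

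**Step 5: power.** Analysed N = 346 × 0.9 × (1 − f), where f is the share without a TWA. Power = Φ[(0.1380 × √(N/2) − 1.0484) / 0.5259], with equal groups.

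| f | N analysed | Power |
|---|---|---|
| 0 | 311 | 90% |
| 2% | 305 | 89% |
| 5% | 296 | 88% |
| 10% | 280 | 87% |
| 13% | 271 | 86% |

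**Step 6: bias.** A simulation on the Step 4 assumptions (600,000 patients per setting) moved the adjusted odds ratio from 3.4 to between 3.2 and 3.4. It also needs a relation between lactate and duration that the documents do not give, so it shows only that no large bias was found.

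**The case against.** Four arguments weigh on the other side.

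- **The post-bypass sample probably counts.** Section 2.4 introduces its whole list of time points, Tn+2 included, as sampling during bypass, and the minimum repeats that phrase. This stands. A reader might take the phrase strictly, leave out Tn+2 and conclude that every run under 120 min is lost, which would remove a large part of the cohort. The section's own usage does not support that as the natural reading. It supports only a request to clarify the phrase.

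- **Other gases may supply a fourth value.** The introduction calls lactate routinely monitored, and section 2.6.4 records arterial gas results from the start of bypass to the end of surgery. Section 2.4 does not say that such values are barred from the count. This stands in part: if they count, fewer patients are lost. But the plan does not say that they count, and the only further lactate samples it provides for are the triggered ones.

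- **Adjustment absorbs much of the selection.** Retention depends on exposure and bypass time, and bypass time is in the adjustment set of section 2.6. This stands, and agrees with the small shift in Step 6.

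- **The size is assumed.** This also stands. Neither the 2–13% nor a particular shortfall in the non-exposure group can be derived from the documents. Groups are formed after measurement, so unequal groups may simply reflect how common raised lactate is.

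**Conclusion.** The concern holds in limited form and is a should-fix. The contradiction itself needs no assumption: section 2.4 asks for four measurements and schedules three for any run under 60 min, and possibly three at about 70–80 min. Together with sections 2.2 and 2.10, this removes eligible patients by rule, and in short runs retention depends on a lactate rise.

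The size does rest on assumptions: about 2–13% excluded and power of about 86–89%, given the stated log-normal bypass times, a 15% rate of triggered samples and equal groups. The consequences are lost patients, power lost beyond the 10% follow-up allowance, and results that apply less well to short elective procedures.

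A reader might infer that the primary odds ratio is seriously biased. Nothing in the documents or the calculations shows that. A reader might also infer from the printed upper limit of the TWA sum that intervals are dropped. That limit is probably a corrupted n − 1, which covers every interval when n is the number of measurements, and it is not part of this point.

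**What to change.** Replace the sentence on the minimum in section 2.4 with:

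> *The minimum is four measurements, or all distinct scheduled samples where the schedule for that bypass duration yields fewer than four, and never fewer than three. The Tn+2 sample counts towards the minimum. Event-triggered extra samples enter the curve but do not count towards the minimum.*

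This keeps short runs in the analysis, settles the phrase about sampling during bypass, and makes inclusion independent of a lactate spike. A looser rule that tolerates one missing hourly sample would not do: a run of 60–119 min has only one hourly sample, so if one of the two end samples could also be missing, TWA could rest on two points.

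The cost is small. TWA rests on three points in short runs, and a few longer runs with a missed scheduled sample are no longer rescued by a triggered one. No extra sampling is needed. The change should be made before exposure and outcome data are seen, because it decides who enters the primary analysis.
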